## Abstract

**Background:** Migraine (MIG) management guidelines support a comprehensive approach combining medication, therapeutic patient education (TPE), behavioral strategies, lifestyle changes, diet, and physical activity (PA). **Objective:** To present an innovative interdisciplinary outpatient model for individuals with MIG, focusing on PA, sedentary behavior, eating habits (EH), metabolic health, temporomandibular disorders, and postural dysfunctions. **Design**: A randomized controlled trial will enroll 200 adults with MIG over two years. Inclusion criteria are chronic MIG (≥15 attacks/month for ≥3 months) or high-frequency episodic MIG (8–14 attacks/month), physical inactivity, and independent walking ability. Exclusion criteria include contraindications to PA and lack of informed consent. Participants will be randomized to standard care (SC) or an intervention group receiving TPE plus three months of supervised exercise (EXE). All participants will receive an informational brochure with nutritional tips (included in SC) and undergo: (1) neurological examination, (2) validated questionnaires, (3) kinesiological and postural assessment, and (4) gnathological evaluation. The primary outcome is change in monthly MIG frequency at 6 and 12 months; additional outcomes include disability, quality of life, and intensity of MIG, PA levels, sedentary behavior, medication use, EH, functional capabilities, postural parameters, and temporomandibular disorder-related variables. **Results**: Hypothetically, the intervention may reduce monthly MIG frequency by approximately 15–20% relative to baseline. Improvements may also occur in disability, quality of life, medication use, lifestyle behaviors, and psychological and cardiometabolic parameters. **Conclusions**: This trial will evaluate whether adding supervised EXE and TPE to SC may improve MIG outcomes compared with SC alone, supporting a comprehensive management strategy.

## 1. Introduction

Migraine (MIG) is a common and disabling neurological disorder characterized by recurrent headaches and a variety of associated symptoms. Neurological disorders are the leading cause of disability globally, affecting 3.4 billion people [1], with migraines being a significant contributor. The prevalence of migraines increased from 732.56 million in 1990 to 1.16 billion in 2021. Particularly, in the 15 to 39 age group, cases rose by 39.52%, from 425.6 million to 593.8 million [2]. This trend is expected to continue, especially among males and adolescents [3,4], and the linked economic impact affects individuals, families, employers, and the broader economy [5]. Its complex pathophysiology involves genetic predispositions, neurovascular dysregulation, and environmental and lifestyle factors, all of which are crucial for informing effective treatment strategies [6,7]. The American Headache Society (AHS) [8], like other headache societies [9,10,11], supports a multidisciplinary approach for the prevention and treatment of MIG. Some authors include acute and preventive pharmacological treatment, therapeutic patient education (TPE), evidence-based behavioral interventions, lifestyle modification [12,13,14], and weight loss strategies [15,16].

In this context, the effects of eating habits (EH) and EXE on MIG management have been studied in several clinical trials [17,18,19]. These studies have demonstrated that dietary patterns may influence MIG through biological mechanisms [20], including modulation of systemic inflammation, oxidative stress, mitochondrial function, and neurotransmitter synthesis [21]. In addition, metabolic conditions that are often associated with an unhealthy diet, such as being overweight or obese and having insulin resistance, have also been linked to an increased MIG frequency and chronicity [22]. The use of standardized tools to assess overall diet quality, such as the diet risk score (DRS), may improve the identification of unhealthy dietary patterns associated with MIG and related metabolic dysfunction [23]. Nutritional factors, such as glycemic load, the intake of ultra-processed foods, and the consumption of bioactive nutrients (like omega-3 fatty acids), may contribute to the onset of MIG [24]. Research suggests that following the Mediterranean diet, rich in anti-inflammatory foods like fruits, vegetables, whole grains, legumes, and olive oil, may lower headache frequency. This effect is likely due to its ability to modulate inflammation and oxidative stress [25,26]. However, the available evidence is not fully consistent, with some studies reporting modest or variable effects. Furthermore, the causal role of specific dietary triggers remains debated. Alongside nutrition, PA has been extensively studied as a non-pharmacological strategy for MIG management; however, no direct comparison of the effectiveness of different EXE interventions has been conducted. Specifically, resistance or strength training appears to offer the greatest benefits in reducing MIG frequency [27]. This effect is likely due to targeted muscle strengthening, particularly in the core muscles of the neck, shoulders, and upper limbs [27]. The observed therapeutic effects may stem from local metabolic and neuromuscular adaptations, along with increased neck strength from resistance EXEs [28]. Regarding aerobic EXE, high-intensity aerobic workouts seem to produce superior effects compared to moderate-intensity workouts. This difference may be linked to the intensity-specific recruitment of endogenous molecules involved in EXE-related pain relief [29]. The dose-dependent impact of aerobic EXE on MIG could be mediated by improved mitochondrial and cardiorespiratory function [30] and the anti-inflammatory mechanisms associated with aerobic activity [31]. Despite these findings, the evidence remains heterogeneous, with variability in EXE type, intensity, and outcome measures, limiting the possibility of definitive conclusions.

Other relevant factors include sleep disturbances (commonly reported in individuals with MIG [32]), psychological comorbidities, temporomandibular disorders (TMDs), and postural dysfunctions, all of which may interact with lifestyle behaviors and contribute to MIG burden. Furthermore, there is increasing evidence of a significant association between temporomandibular disorders (TMDs) and primary headache [33]. People with headaches may exhibit postural alterations not only in the craniocervical region but also throughout the spine. TMDs involve various conditions affecting the masticatory muscles, temporomandibular joints, and related anatomical structures. Although several studies suggest that dietary patterns and PA may influence the frequency and severity of MIG, the current evidence remains inconsistent. Differences in study design, intervention protocols, and outcome measures limit the comparability of the findings, with some studies reporting modest or inconsistent effects.

Overall, the strength of evidence supporting integrated multidisciplinary approaches is still limited, as most studies focus on single interventions rather than combined models [34,35,36,37]. Despite the multidisciplinary and patient-centered approach to headache management in primary care showing significant benefits on outcomes and quality of life, the literature is not unanimous regarding the number and the typology of healthcare disciplines and professionals to involve, particularly those linked to nonpharmacological treatments [38]. In fact, research in this area is limited, and few studies adopt a structured interdisciplinary approach: some studies include neurologists, psychologists, and physiotherapists, while other studies also involve dentists or nurses (please see Table 1). For these reasons, there is a need for validated interdisciplinary models designed to enhance structured lifestyle-related assessment and interventions, with a specific focus on PA for individuals suffering from chronic, episodic, and high-frequency MIG.

This manuscript describes the model of the project “*Study of the effects of a multidisciplinary intervention-including physical exercise-in people with high-frequency episodic migraine and chronic migraine*”, or EXEMIG/01, an innovative model for the prevention and treatment of chronic or episodic and high-frequency MIG, based on the AHS principle of an interdisciplinary team approach. Different from previous studies, the EXEMIG/01 model integrates Migraines and Headaches Center standard care, adding an interdisciplinary structured team involving different specialists’ competence in support of the neurologist, adapting the validated C.U.R.IAMo. (Centro Universitario Ricerca Interdipartimentale Attività Motoria of the Department of Medicine and Surgery of Perugia University) work methodology [51,52]. In fact, in this model, we include EXE, nutritional assessment, postural, and gnathological evaluation. This model aims to study multiple determinants of MIG in a tailored and structured clinical manner.

## 2. Materials and Methods

The EXEMIG/01 study is a randomized, controlled interventional trial designed to present an interdisciplinary model (Figure 1) to prevent and manage MIG.

The primary outcome of the study is the change in monthly MIG frequency (number of MIG/month) from baseline at 6 and 12 months. The secondary outcomes include: MIG-related disability, MIG-specific quality of life (MSQoL), MIG intensity, PA levels and sedentary behavior, medication use (number of doses/month), dietary adherence, functional capabilities, postural parameters, and temporomandibular disorder-related variables. Exploratory measures include sleep quality, anthropometric measurements, metabolic parameters, cardiometabolic risk, psychological and psychopathological factors associated with MIG. Ultimately, the project aims to improve the treatment and management of people with MIG by providing educational material addressing known health risk factors, such as unhealthy EH (through an informational brochure given to all participants), a sedentary lifestyle, and physical inactivity.

The EXEMIG/01 trial is registered in the Clinical Trials Registry (ClinicalTrials.gov) with the identifier NCT07508449, and it was approved on 18 September 2024 by the local Ethic Committee (Comitato Etico Regionale dell’Umbria) with the protocol number CET N.4807/24.

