#### 2.2.4. Phase 4: The Follow-Up

All evaluations will be re-executed after six (T1) and twelve (T2) months from the start of the study. During follow-up appointments, we will update specific process variables, described below.

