### 2.4. Statistical Analysis

The primary efficacy analysis will be performed in the intention-to-treat (ITT) population. The pre-protocol population consisted of all patients in the ITT population without major protocol deviations and will be used for the supportive analysis of the primary efficacy endpoint.

The quantitative data collected, organized into two distinct groups of subjects, will be presented in tables that include the mean and standard deviation. In addition, qualitative data will be represented through frequency distributions.

The primary endpoint (number of MIGs/month from baseline to 6 and 12 months) will be analyzed using a linear mixed-effect model (LMEM) with treatment group × time as the fixed effect and the baseline number of MIG/month value as the covariate.

For qualitative data analysis, the Chi-square test will be implemented.

The scores obtained from the evaluation scales will be correlated with the clinical parameters of the participants, when applicable, using the Pearson or Spearman correlation coefficients, contingent upon the distribution of the data.

In the case of individuals with MIG, a logistic regression analysis will be performed to investigate potential associations between psychopathological parameters and the response to headache treatment. Adherence to both PA and TPE will be incorporated as process variables in the analyses. Dietary adherence scores from the Mediterranean Diet Assessment Tool, Diet Risk Score, and food-headache diaries will be assessed longitudinally for their potential as predictors of migraine outcomes. Additionally, EXE adherence will be evaluated through attendance records and wearable device data.

Analyses will be limited to participants with complete data on different measurements. We hypothesized that missing data occur randomly into two group. We plan to gather additional information from participants who drop out.

Should the dropout rate exceed our projections, we will employ a regression model to impute the missing data.

The exploratory outcomes will be evaluated utilizing the same LMEM employed for the primary analysis, without adjustments for multiple comparisons. Conclusions will be derived from effect size estimates, specifically Cohen’s d, accompanied by a 95% bootstrap confidence interval (CI). Effect sizes will be systematically classified as small (d = 0.2), medium (d = 0.5), and large (d = 0.8).

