All statistical analyses will be completed using IBM SPSS^®^ Statistics for Windows version 25.0 (IBM Corp., Armonk, NY, USA).

*Sample Size.* The sample size calculation was based on real-life data regarding the response rate to therapy through PA in people with MIG, specifically focusing on the number of headache days. According to the literature, this approach indicates a decrease of approximately 15–20% relative to baseline data [98]. To determine the number of participants in the intervention and control groups, we referenced various articles on the subject, particularly the work of Krøll et al. [98,99], which indicates that the average difference in the number of headache days is almost 2 days less than the baseline. The standard deviation is estimated to be approximately 50% of the average for both groups. Assuming a 1:1 ratio, with a significance level of 5% and a statistical power of 80%, a sample size of a total of around 200 participants (100 patients per group) will be determined, accounting for an anticipated dropout rate of 30%. The recruitment of this cohort will be scheduled for over 9 months to effectively achieve the desired enrollment.

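### The primary outcome is set at both 6 and 12 months, but the single 5% level and 80% power are tied to neither visit and no rule says which visit decides

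*Protocol article*

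**What the plan says.** The Abstract ("The primary outcome is change in monthly MIG frequency at 6 and 12 months") and section 2, Materials and Methods ("The primary outcome of the study is the change in monthly MIG frequency (number of MIG/month) from baseline at 6 and 12 months") name the same two time points. Section 2.4, Statistical Analysis, repeats them: "The primary endpoint (number of MIGs/month from baseline to 6 and 12 months". Section 2.2.4 shows that they are two separate visits: "All evaluations will be re-executed after six (T1) and twelve (T2) months from the start of the study".

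For the analysis, section 2.4 specifies a "linear mixed-effect model (LMEM) with treatment group × time as the fixed effect and the baseline number of MIG/month value as the covariate". It names no contrast from that model as the deciding one. Its only statement on multiplicity concerns other outcomes: "The exploratory outcomes will be evaluated utilizing the same LMEM employed for the primary analysis, without adjustments for multiple comparisons".

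The Sample Size paragraph of section 2.4 works from a single comparison: "Assuming a 1:1 ratio, with a significance level of 5% and a statistical power of 80" per cent. It gives an effect of almost 2 headache days, an SD of about half the mean, and 100 per group including 30% dropout. None of these inputs is attached to 6 or 12 months.

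**The concern.** Two visits give two between-arm differences, and a trial with two primary answers needs a rule for combining them. Without one, the stated design figures have no definite meaning. If success at either visit is enough, the 5% level is exceeded. If success at both is needed, the 80% power, which belongs to one comparison, does not apply.

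The two answers could well differ. Supervised exercise lasts 12 weeks (section 2.2.3), so the 6-month visit falls about three months after supervision ends and the 12-month visit about nine months after. A benefit present at the first visit and gone at the second would fit the text as a success or as a failure. The trial is unblinded with a self-reported primary outcome, and the Discussion itself warns that the effect may be overestimated, so the deciding comparison should be fixed in advance.

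**Working it through.** **1. The plan's own figure.** Inputs from the Sample Size paragraph: difference 2 days; 15–20% of baseline, so the implied mean is 2/0.20 = 10 to 2/0.15 = 13.3 days; SD 50% of the mean, so 5.0 to 6.67; 5% (sidedness not stated, two-sided assumed here); power 80%; 1:1.

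n per arm = 2(1.960 + 0.842)² × SD² / difference². With SD 5 this is 2 × 7.849 × 25/4 = 98.1, so 99 per arm and 198 in total. That agrees with the stated 200 for one comparison, but before dropout. Allowing for 30% dropout, 99/0.70 gives 142 per arm. That discrepancy is a separate issue. It matters here only because the power below must be shown for both 100 and 70 evaluable per arm.

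**2. Does the model supply a rule?** Baseline enters as a covariate, so it is not one of the outcome rows and time has two levels, 6 and 12 months. The group × time interaction then tests whether the treatment effect differs between the two visits. It does not test whether there is an effect. A treatment claim must come from the 6-month contrast, the 12-month contrast, or a joint or averaged contrast, and the article chooses none of them.

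**3. If either visit counts.** The false-claim chance is P(|Z6| > 1.96 or |Z12| > 1.96) = 0.05 + 0.05 − P(both exceed 1.96), with the two statistics bivariate normal with correlation r. The article gives no r, so a range is shown:

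| r (assumed) | P(both exceed) | False-claim chance |
|---|---|---|
| 0 | 0.0025 | 9.75% |
| 0.3 | 0.0049 | 9.5% |
| 0.5 | 0.0093 | 9.1% |
| 0.7 | 0.0165 | 8.35% |
| 0.8 | 0.0219 | 7.8% |
| 0.9 | 0.0296 | 7.0% |
| 1 | 0.05 | 5.0% |

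A null simulation (20,000 runs, 70 per arm, baseline-adjusted, equal correlations of 0.3, 0.5 or 0.7 among the three visits) gave 9.7%, 9.3% and 9.1% for the either-visit rule. In the same runs the both-visits rule gave under 1%, and a joint or averaged test gave about 5%.

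**4. If both visits must succeed.** Assume a difference of 2 at each visit and SD 5. The expected Z is 2/(5√(2/n)), which is 2.83 for n = 100 and 2.37 for n = 70. Power for one contrast is Φ(Z − 1.96); power for both is the bivariate normal probability that both exceed 1.96.

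| n per arm | One contrast | Both, r = 0.5 | Both, r = 0.7 |
|---|---|---|---|
| 100 | 80.7% | 69.7% | 72.2% |
| 70 | 65.8% | 50.6% | 54.2% |

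Requiring both therefore costs about 9 to 11 points at 100 per arm and about 12 to 15 points at 70 per arm. SD 5 is the favourable end of the implied range. At SD 6.67, power for one contrast alone is already 56% (n = 100) or 43% (n = 70).

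**The case against.** The strongest reply is that the article names one mixed model, not two tests, and that it condenses a fuller protocol and perhaps an analysis plan that are not shown. The deciding contrast and any order of testing may be written there. The part that stands is that it cannot be claimed that the verdict will be chosen after the data are seen.

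The reply does not remove the point. Which time point is primary belongs to the definition of the endpoint, and the article gives that definition three times, each with two visits. It attaches one significance level and one power to the pair. The one model it names does not yield a single treatment test as described.

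A reader might infer that the trial's error rate is about 8–9% instead of 5%. The documents do not support that. It needs an either-visit rule, which the article does not state, and a correlation of about 0.53 to 0.77, which it does not give. Read with the printed "and" as requiring both visits, the error is below 5%; with one joint or averaged test it is about 5%.

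A reader might also set 51–54% power against the stated 80%. That charges the two visits with a loss that is partly due to dropout, because one contrast at 70 per arm already has only 66%.

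**Conclusion.** The point holds in a conditional form. The article fixes two primary time points under one 5% level and one 80% power, with no deciding rule, so at least one of those two figures fails unless a joint or averaged test that the text does not name is used.

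Under an either-visit rule at two-sided 5% each, the false-claim chance is above 5% for any correlation below 1 and never more than 9.75%. Under a both-visits rule the error is controlled, but power is about 70–72% instead of 81% at 100 per arm, or 51–54% instead of 66% at 70 per arm. The power figures rest on an assumed difference of 2 at both visits, SD 5 and correlation 0.5–0.7. The defect can be repaired credibly only before outcome data by arm are examined.

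**What to change.** In section 2 and in section 2.4, name the between-arm contrast from the mixed model at one of the two visits as the primary test, and tie the Sample Size paragraph to that visit. Test the other visit at 5% only if the first is significant (fixed sequence). Report the between-arm difference with its 95% CI at both visits whatever the test results. Make the Abstract and the registry entry agree.

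One prespecified joint or averaged 6/12-month contrast would also hold the 5% level. Requiring both visits would do so too, but the sample size would then need to be recalculated. Splitting alpha to 2.5% per visit is valid but dearer: at SD 5 it needs 119 evaluable per arm instead of 99.

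The recommended change costs a sentence or two, with no added patients or visits. Its downside is that the second time point can no longer rescue a failed first one.

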### 2.1. Study Design

The EXEMIG/01 study was a rigorously designed, randomized, controlled, non-blinded interventional trial. This study is non-blinded due to the nature of the intervention, which may introduce performance and assessment bias, particularly with regard to self-reported outcomes. To minimize this risk, standardized procedures, validated questionnaires, and objective measures (e.g., wearable accelerometers) will be used wherever possible.

A total of 200 individuals suffering from episodic high-frequency or chronic MIG (diagnosed following the international criteria outlined in the ICHD Classification 2018 [53]) will be invited to participate voluntarily in this project. Participants will be selected from those attending the Headache Center at Santa Maria della Misericordia Hospital in Perugia, following the usual CUP booking procedures for a neurological consultation. The inclusion criteria were as follows: chronic (≥15 attacks/month, for at least 3 months) or episodic and high frequency (8–14 attacks/month) MIG; age range 18–65 years; PA levels lower than WHO recommendations (engage in 150 to 300 min of weekly moderate-intensity aerobic PA, or 75 to 150 min of vigorous-intensity aerobic activity, or a combination of both that is equivalent [54]); and ability to walk independently. The exclusion criteria were as follows: age younger than 18 years or older than 65 years; clinical evidence of serious cardiovascular, central nervous system, or significant musculoskeletal disease that may limit or contraindicate EXE; and failure to provide written consent for participation in the study.

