### 2.2. Project Phases

#### 2.2.1. Phase 1: Enrollment and Medical Assessment

All participants will be invited to attend their first specialist visit to the Headache Center of the Santa Maria della Misericordia Hospital in Perugia. The neurologist conducts a thorough interview covering the onset and evolution of the headache, its frequency, duration, and intensity, associated symptoms (nausea, vomiting, photophobia, phonophobia), presence of aura, triggering and relieving factors, family history, sleep quality, stress levels, and menstrual cycle in women.

During the neurological assessment, we will collect comprehensive information for each participant, including age, sex, age of headache onset (in years), potential onset of MIG chronicity (in years), existing comorbidities, other medications being utilized, and symptomatic medications used as needed (with a focus on their efficacy). Furthermore, we will gather details regarding prophylactic medications (usage timing, dosage, potential side effects, and effectiveness: yes/no assessed as a reduction of at least 50% of attacks after at least 3 months of treatment compared to the pre-treatment period) along with the characteristics of the headaches (presence of aura, occurrence of other primary headaches, and frequency of headaches experienced in the past three months). Moreover, blood test results and any previous neuroimaging are reviewed to exclude secondary causes of headache and to assess comorbidities relevant to treatment decisions.

Based on all collected data, the neurologist formulates a diagnosis following the International Classification of Headache Disorders (ICHD-III, 2018) [53], distinguishing between migraine (with or without aura), chronic migraine (≥15 headache days/month for >3 months), tension-type headache, medication overuse headache, and other primary or secondary headache disorders. The neurologist also formulates a personalized treatment plan including acute medications, preventive pharmacological therapy (e.g., beta-blockers, antiepileptics, calcitonin gene-related peptide (CGRP) monoclonal antibodies), and non-pharmacological strategies (lifestyle modifications, biofeedback, physical therapy referral). During this phase, participants will receive detailed information about the project, and an informed consent form, along with a data processing form, will be presented for their signature.

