### 2.3. Measures

#### 2.3.1. Phase 1: Medical Assessment

Participants will be invited to complete an online questionnaire to collect information about age, sex, years of illness, presence (or not) of MIG aura, frequency of headache attacks (number of attacks per month), intensity of the MIG episodes (measured using a 10-point numerical rating scale), and number of headache attacks per month (tracked using diaries provided to the participant). Moreover, dose and type of symptomatic and prophylaxis drugs used monthly by participants will be recorded.

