## 3. Expected Results

As this is a study protocol, no actual results are currently available. The following section outlines the study’s hypotheses and anticipated outcomes based on existing evidence. According to the current literature, the proposed interdisciplinary intervention, primarily based on supervised physical EXE and TPE, is hypothesized to improve clinical outcomes in individuals with MIG (e.g., frequency) and may also contribute to improvements in lifestyle-related outcomes and overall disease burden [100].

Regarding the primary outcome, the study aims to evaluate whether the intervention is associated with a reduction in MIG frequency. It is hypothesized that the intervention group may show a decrease in monthly headache days of approximately 15–20% compared with baseline [98]. This assumption is in line with previous evidence, including studies by Krøll et al. [98,99], which reported an average reduction of about two headache days per month in people engaging in PA interventions.

Regarding the secondary outcomes, in accordance with previous studies [14,17,62], we hypothesize that the intervention may be associated with improvements in MIG-related disability, MSQoL, MIG intensity, PA levels, and sedentary behavior, medication use (number of doses/month), dietary adherence, functional capacity, and postural and temporomandibular function, in line with the intervention’s interdisciplinary nature [101]. With respect to explorative measures, potential improvements may be observed in sleep quality [102], weight and WC [103,104], and key cardiometabolic parameters (including fasting glucose, HbA1c, lipid LDL, HDL, triglycerides, blood pressure, and CRP) and related risk, which may reflect changes in systemic inflammation and cardiometabolic risk, particularly among participants in the supervised EXE program [105,106]. However, these outcomes will be explored and require confirmation.

Additional benefits are anticipated in other areas, including anxiety and depression symptoms, and kinesiophobia. A reduction in allodynia scores is also hypothesized, suggesting a potential modulation of central sensitization mechanisms [107].

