For the previous considerations, an interdisciplinary approach, involving professionals such as neurologists, dieticians, kinesiologists, and gnathologists, allows for a more comprehensive assessment and may act on multiple aspects relevant to MIG management. This approach could promote greater treatment adherence, reducing dependence on medication and improving quality of life, laying the foundation for stable and lasting change in the lifestyle of individuals with MIG. In this context, TPE serves as a crucial resource for enhancing people’s awareness. It encourages individuals to recognize their specific triggers and fosters the development of self-management skills [126,127]. Our protocol is designed to evaluate whether a reduction of approximately 15–20% in monthly attacks and improvements in clinical metrics can be achieved. The goal is not only to achieve immediate clinical benefits but also to encourage long-lasting lifestyle changes among participants.

Additionally, our study could contribute to the development of a potentially replicable interdisciplinary model that can be applied in headache centers and in general medicine and rehabilitation settings. It also aims to promote the implementation of the EXE recommendations. However, there are potential limitations to consider.

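### Eligibility is set in attacks per month, the chronic migraine diagnosis and the sizing use headache days, and the unit of the primary endpoint is not settled

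*Protocol article*

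**What the plan says.** **Eligibility.** The Abstract and section 2.1 set the thresholds in attacks: "chronic (≥15 attacks/month, for at least 3 months) or episodic and high frequency (8–14 attacks/month) MIG". Section 2.1 also requires diagnosis by the 2018 international classification.

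**Diagnosis.** Section 2.2.1 cites the same classification and has the neurologist apply "chronic migraine (≥15 headache days/month for >3 months".

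**Primary outcome.** Section 2 defines it as "the change in monthly MIG frequency (number of MIG/month) from baseline at 6 and 12 months", and section 2.4 models the same quantity. Neither says whether the count is of attacks or of days.

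**Measurement.** Section 2.3.1 collects "frequency of headache attacks (number of attacks per month" by questionnaire and "number of headache attacks per month (tracked using diaries provided to the participant" by diary. It lists no count of headache days.

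**Sizing and target.** The sample size paragraph in section 2.4 rests on therapy response, "specifically focusing on the number of headache days". It assumes a 15–20% reduction, about two days below baseline, and an SD of about half the mean. Section 3, when it turns to the primary outcome, says "the intervention group may show a decrease in monthly headache days of approximately 15–20% compared with baseline". The Discussion says "Our protocol is designed to evaluate whether a reduction of approximately 15–20% in monthly attacks".

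**The concern.** An attack is an event and a headache day is a unit of time. The article itself treats them as different things, because frequency and duration are recorded separately in the neurologist's interview (section 2.2.1) and the food-headache diary records the duration of each attack (section 2.3.2). Where an attack can last more than one day, the two counts differ.

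Three things depend on the unit:

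- who may enter;
- what the primary endpoint counts;
- which variable the planned two-day effect refers to.

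An open unit also leaves room to choose days or attacks after the data are seen. That matters more here because the trial is unblinded and the outcome is self-reported.

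**Working it through.** **1. The places side by side**

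| Element | Where | Unit |
|---|---|---|
| Entry thresholds | Abstract, 2.1 | attacks |
| Chronic migraine diagnosis | 2.2.1 | headache days |
| Primary endpoint | 2, 2.4 | not specified |
| Data collected | 2.3.1 | attacks |
| Sample size | 2.4 | headache days |
| Primary hypothesis | 3 | headache days |
| Stated aim | 4 | attacks |

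The same 15–20% target is attached to days in two places and to attacks in one. No section equates the units.

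**2. Eligibility**

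Let k be the mean number of headache days per attack. The article gives no value, so k is an assumption. Attacks = days / k. For a patient with exactly 15 headache days per month:

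- k = 1: 15 attacks. Chronic under both definitions.
- k = 2: 15 / 2 = 7.5 attacks. With 7 attacks the patient is ineligible. With 8 the patient is eligible, but in the episodic band.
- k = 3: 15 / 3 = 5 attacks. Chronic under section 2.2.1, ineligible under section 2.1.

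In the other direction, 8–14 attacks at k = 2 are 16–28 headache days. Such patients meet the day threshold for chronic migraine but fall in the episodic band of section 2.1. They are eligible either way.

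**3. The plan's own sample size**

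Inputs from section 2.4: effect 2 days, 15–20% of baseline, SD half the mean, 1:1 allocation, 5% significance (taken as two-sided), 80% power. At 20% the implied mean is 2 / 0.20 = 10 days and the SD is 5.

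n per group = 2 × (1.960 + 0.842)² × (SD / effect)² = 2 × 7.849 × (5 / 2)² = 98.1, rounded up to 99.

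That is 198 in total, which matches the planned 200 only before the 30% dropout allowance. The dropout allowance is a separate matter and plays no part in this point.

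**4. The relative effect does not depend on the unit**

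With effect 0.20 × mean and SD 0.50 × mean, SD / effect = 0.5 / 0.2 = 2.5 whatever the mean is. The result is 99 per group in days or in attacks. At 15% the ratio is 0.5 / 0.15 = 3.33, giving 175 per group in either unit. This assumes that the SD is half the mean for attacks too, and that treatment changes days and attacks by the same percentage.

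**5. The absolute effect does depend on the unit**

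Two days = 2 / k attacks. If the SD also shrinks to 5 / k, n stays at 99. If the SD stays at 5 (an assumed mean of 10 attacks per month), then n = 2 × 7.849 × (5k / 2)²:

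| k (assumed) | Effect in attacks | n per group before dropout, SD kept at 5 | Power with 100 per group |
|---|---|---|---|
| 1 | 2.0 | 99 | 81% |
| 1.5 | 1.33 | 221 | 47% |
| 2 | 1.0 | 393 | 29% |
| 3 | 0.7 | 883 | 16% |

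**The case against.** The strongest reply has four parts.

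- **Endpoint unit.** The endpoint definition does not use the word attacks, and section 3 states the primary hypothesis in headache days, the sizing unit. A reader might infer that the endpoint plainly counts attacks and so is not what the trial was sized on. The text does not support that. It supports only that the unit is unsettled, with section 2.3.1 and the Discussion pointing one way and sections 2.4 and 3 the other.
- **Power.** A reader might infer that the planned effect cannot apply and that the trial is underpowered for this reason. On the relative scale the sample size is the same in either unit. The losses in the last table arise only if the absolute effect shrinks while the SD does not.
- **Selection.** A reader might infer that the wrong patients will be enrolled or misclassified. The neurologist applies the headache-day definition, both frequency bands are eligible, and nothing shown uses chronic versus episodic status for stratification or in the primary model. The demonstrated harm runs one way: some patients with few, long attacks are shut out. How many cannot be said, because days per attack is not given.
- **Choice of unit.** Keeping attacks would be equally consistent if the effect and SD were justified in attacks.

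All four stand as limits on the point. None removes the contradiction. The relative argument also has a limit of its own: shorter attacks would lower the number of days without lowering the number of attacks, so equal percentage effects cannot be taken for granted.

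**Conclusion.** The inconsistency is in the text and needs no assumption. Entry is in attacks, the chronic diagnosis is in headache days, and the primary endpoint has one target expressed in two units. It is a contradiction between stated passages, so it cannot be put down to detail left for an analysis plan.

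Two consequences follow wherever attacks last more than a day. Patients with at least 15 headache days in fewer than 8 attacks are chronic by the article's own definition but ineligible. The two-day effect becomes 1.0 or 0.7 attacks at an assumed 2 or 3 days per attack.

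A loss of power is possible but conditional. It ranges from none, if SD and effect scale together, to a fall from 81% to 29% with 100 per group, at an assumed 2 days per attack and an SD held at 5.

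**What to change.** Choose one unit, define it (what counts as a headache day or as an attack, and over what period), and use it for eligibility, primary endpoint, diary count, planned effect and SD. The places to reconcile are the Abstract, sections 2, 2.1, 2.2.1, 2.3.1, 2.4 (model and sample size) and 3, and the Discussion.

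Headache days per month is the natural choice because the diagnosis and the sizing already use it. The attack count can stay as a secondary outcome. If attacks remain primary, restate the effect and SD in attacks, with a source for both.

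**Cost.** The change touches eligibility and the primary endpoint of a registered, ethics-approved trial, so it needs a protocol amendment and a registry update. The diary must capture headache days over the full month. The food-headache diary in section 2.3.2 covers seven days; if that is the diary meant in section 2.3.1, it has to be extended. No extra visits are needed.
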